#### Data Collection

Age (years), gender, weight (kg), height (cm), body mass index (BMI) (kg/m^2^), main diagnosis, clinical history, and illness severity assessed using the Acute Physiology and Chronic Health Evaluation (APACHE) II score [15] will be collected at time of admission in ICU (baseline assessment). The Simplified Acute Physiology Score (SAPS) II for mortality prediction in ICU [16] will also be calculated.

The following parameters will be recorded at midnight of each day: caloric intake, protein intake, measurement of 24-hour urine urea nitrogen (UUN) excretion, blood creatinine, NB, blood urea nitrogen (BUN) level, average blood glucose, amount of propofol administered (mL/day), amount of dextrose administered (mL/day).

A standard formula will be used for NB calculation [17,18]: total protein intake (g)/6.25 –(UUN + 4 g), where 6.25 = 6.25 g of protein per gram of nitrogen, UUN = grams of nitrogen excreted in the urine over 24-hour period of time, and 4 = 4 g of nitrogen lost each day as insensible losses via the skin and gastrointestinal tract. Additionally, for each patient, the duration of mechanical ventilation and any infection or skin alteration discovered during the study period will be reported.

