**Results:**

Enrollment began in January 2017. In the feasibility study, 14 patients were enrolled. Protein administration increased significantly (*P*<.001) over time but was significantly lower compared to that recommended (*P*<.001). Blood urea nitrogen significantly increased (*P*<.03) over the period of observation. Such increased catabolism resulted in negative cumulative nitrogen balance (NB) in all patients, and some patients presented with a more negative NB compared to the others.

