### Feasibility Study

Sample characteristics are summarized in Table 1. A total of 14 patients were enrolled, with a median age of 48 years. Median weight was 83 kg, and median BMI was 25.5 kg/m^2^. For about a half of the patients (6/14, 43%) the main diagnosis reported at time of admission was trauma (especially multiple trauma). Of the 14 patients evaluated, 8 (57%) completed the observation until the end of mechanical ventilation.

Figure 2 shows the contribution of EN, PN, extra proteins (represented by albumin), and propofol and dextrose infusions to the mean energy (kcal) intake over the feasibility study period. During the first 3 days of observation, propofol contributed to about half of the daily caloric intake. Additionally, calories introduced by PN increased over the days, while calories provided by EN remained stable. Overall, caloric intake increased over time. Along with caloric intake, protein administration also increased significantly (*P*<.001) over the period of observation (Figure 3).

Despite the increased provision of protein during hospitalization, the BUN significantly increased (*P*=.03) over the period of observation (Figure 4), thus indicating an increased catabolism in patients enrolled (since urea represents the waste product from protein metabolism). Increased catabolism resulted in negative NB, as shown in Figure 5. All patients had a negative cumulative NB in the first 72 hours of observation, and some patients presented with a markedly more negative NB compared to the others.

Finally, Figure 6 reports the comparison between patients’ actual protein intake and that recommended by international guidelines (considering a value of 1.8 g/kg/day in the range between 1.2 and 2 g/kg/day). Clearly, the amount of protein actually administered is significantly lower compared to that recommended (*P*<.0001) (for patient 7, PN/EN was not administered in the first 24 hours due to medical procedures, resulting in fasting). The median difference between actual and recommend protein intake was found to be –360 g/kg (range –638 to 52).

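### The nitrogen balance formula has no term for change in the body urea pool, so the primary comparison is at risk of bias, most plausibly toward the protein-fortified arm, if BUN rises more there

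*Protocol article*

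**What the plan says.** The trial's Data Collection section defines the outcome: "A standard formula will be used for NB calculation [17,18]: total protein intake (g)/6.25", minus the sum of UUN and 4 g for skin and gastrointestinal losses. UUN is limited to what leaves in urine: "UUN = grams of nitrogen excreted in the urine over 24-hour period of time". The same section lists the values recorded at midnight each day, among them "blood creatinine, NB, blood urea nitrogen (BUN) level, average blood glucose". BUN is therefore collected daily but does not enter the formula. Sample Size makes NB the primary outcome, and Statistical Analysis Plan compares it between arms with a t test.

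In the Feasibility Study results, "the BUN significantly increased (*P*=.03) over the period of observation". The article reads this as catabolism, "since urea represents the waste product from protein metabolism". All feasibility patients received the standard diet, and the size of the rise appears only in a figure that is not shown.

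**The concern.** By mass balance, nitrogen taken in is either retained as protein, lost, or held for a time as urea in body water. The formula counts the third part with the first. It equals true retention only while the urea pool is stable, and the trial's own feasibility data suggest that the pool may not be. There is an internal tension as well: the article takes a rising BUN as a sign of protein breakdown, while its NB formula credits that same urea as nitrogen kept.

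The arm given more nitrogen is likely to form more urea. If some of it accumulates rather than being excreted, the t test scores it as benefit. The error would be systematic, so neither randomization nor sample size removes it. A positive result could not then be split into spared protein and urea still waiting to be excreted.

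**Working it through.** **1. The plan's own figure.** Inputs from Sample Size: difference 6 g, SD 5 g, alpha .025, power 0.90, 1:1 allocation. Normal approximation, two-sided: n = 2 × (5/6)² × (2.2414 + 1.2816)² = 17.2, so 18 per arm. The exact t calculation gives 19 per arm (power 0.908), which reproduces the stated 19. One-sided .025 gives 15 or 16 and does not. The sample size is not in error on this point.

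**2. The omitted term.** Uncounted urea N (g) = BUN change (mg/dL) × 0.01 × body water (L). Weight is the feasibility median, 83 kg. Body water of 0.5-0.6 L/kg is an assumption and gives 41.5-49.8 L.

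- Per 1 mg/dL: 0.01 × 41.5 to 0.01 × 49.8 = 0.42-0.50 g N.
- At the weight quartiles: 0.33-0.40 g (66 kg) and 0.47-0.56 g (94 kg).

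**3. Direction.** Nominal full enteral feeding at 83 kg, from Treatment Arms:

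- Control, lowest: 20 × 83 = 1660 kcal at 1.5 kcal/mL and 40 g/L = 44.3 g protein; /6.25 = 7.1 g N/day.
- Control, highest: 25 × 83 = 2075 kcal at 1 kcal/mL and 40 g/L = 83.0 g protein; /6.25 = 13.3 g N/day.
- Intervention: 1.2 × 83 = 99.6 g to 2 × 83 = 166 g protein; /6.25 = 15.9-26.6 g N/day.

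The intake gap is 2.7-19.5 g N/day. At 1.8 g/kg (the value used in the feasibility comparison) against the highest control intake, it is 23.9 − 13.3 = 10.6 g/day. If 6 g of that were truly retained, about 4.6 g/day more urea N would be formed in the intervention arm. Only the part not yet excreted enters the error. The intervention arm also aims for its energy goal sooner (48 versus 72 hours), when the urea pool is likely to be changing.

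**4. Size for assumed between-arm differences in total BUN rise** (83 kg, 0.5-0.6 L/kg):

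| Difference in BUN rise | Cumulative NB | Per day over 3 days | Per day over 8 days |
|---|---|---|---|
| 5 mg/dL | 2.1-2.5 g | 0.7-0.8 g | 0.3 g |
| 10 mg/dL | 4.2-5.0 g | 1.4-1.7 g | 0.5-0.6 g |
| 20 mg/dL | 8.3-10.0 g | 2.8-3.3 g | 1.0-1.2 g |

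Eight days is the median feasibility observation period; 72 hours is the cumulative window its NB results use. The article does not fix which form of NB the t test compares. On a single day, a difference of 6/0.498 = 12.0 to 6/0.415 = 14.5 mg/dL would by itself equal the 6 g target.

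**5. Effect on the test.** With 19 per arm, SD 5 g, two-sided alpha .025 and no true effect, a spurious difference of b g gives noncentrality (b/5) × √(19/2):

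| b | Rejection rate |
|---|---|
| 0 | 2.5% |
| 0.5 g | 3.2% |
| 1 g | 5.2% |
| 2 g | 14.7% |
| 3 g | 32.4% |

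These rates apply only if the SD of 5 g belongs to the same form of NB as b.

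**The case against.** A reader might infer that the primary outcome is biased toward the intervention. The documents do not show this. Only a between-arm difference in BUN change shifts the t test, and the only BUN data are single-arm, on the standard diet. If the intervention reduced catabolism enough, as intended, the error could even reverse.

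The feasibility trend is also weak evidence. It is a Spearman test of daily means against time (Data Analysis). Patients left at different times, and 3 of 14 exited with acute renal or hepatic failure, so the trend may partly reflect who remained or a few patients with failing kidneys. The trial excludes KDIGO stages 2 and 3 at entry.

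A reader might also put a large share of the 6 g target on this error. A gap of 3-5 mg/dL per day would give 1.2-2.5 g/day, or 21-42% of 6 g. Sustained for 8 days, however, it means the arms diverge by 24-40 mg/dL, and nothing in the documents supports that. Nor should a 10 mg/dL rise within one patient, worth 4.2-5.0 g, be read as a between-arm bias.

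Finally, the article calls its formula standard and cites sources for it, sensitivity analyses are commonly left to an analysis plan that is not shown, and enrollment had begun.

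All of this limits the claim and the remedy. It does not remove the point: the formula is fixed in the article, its omission follows from mass balance, and no other passage deals with it.

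**Conclusion.** The point holds as a risk of bias, not as demonstrated bias. The stated NB scores accumulating urea as retained nitrogen. The most plausible direction favours the protein-fortified arm, because that arm is expected to form more urea. This rests on BUN rising more there, which the documents neither show nor exclude.

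The scale is 0.42-0.50 g N per 1 mg/dL of between-arm difference in BUN rise, assuming 83 kg and body water of 0.5-0.6 L/kg. The consequence runs from minor to comparable with the design difference. A 5-10 mg/dL difference averaged over 8 days is 0.3-0.6 g/day and moves the null rejection rate from 2.5% to about 3%; 10 mg/dL counted cumulatively over 72 hours is 4.2-5.0 g.

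Should-fix, with moderate confidence. A reader might conclude that the primary endpoint must be replaced. The case does not reach that far, since the assumed 6 g difference and 5 g SD accompany the stated NB and enrollment is under way.

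**What to change.** Keep the stated NB as the primary endpoint. Before database lock, prespecify as a key sensitivity analysis:

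NB = protein/6.25 − [UUN + (BUN at end − BUN at start, in g/L) × body water (L) + 4]

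Use the daily midnight BUN and the admission weight already recorded, with one fixed body-water fraction in both arms, checked at 0.5 and 0.6 L/kg. Report corrected and uncorrected NB side by side, together with BUN change by arm. State in advance that an NB gain will be attributed to spared protein only if it persists after correction. The correction works whichever way BUN moves.

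The cost is small: a derivation and one further analysis, with little or no new data. There are three drawbacks. A fixed body-water volume ignores fluid shifts during the ICU stay: fluid gain dilutes BUN and hides accumulation, and varying the fraction does not address this. The extra term adds some measurement noise. The admission list names no BUN, so the first day may lack a starting value; where it does, begin the corrected calculation at the first midnight value and show uncorrected NB for the same days.

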#### Sample Size

Considering NB as primary outcome, a sample size estimation has been performed considering a *t* test difference in means between the 2 groups (standard and protein-fortified diet). For a specified alpha of .025 and a power of 0.90, which aimed at detecting a difference of at least –6 g of NB between the 2 groups (assuming an equal standard deviation in the 2 groups of 5 g), the estimated sample size is 19 per arm for a total of 38 patients to be randomized. The sample size has been estimated using the sample size package in R software (The R Foundation) [19].

Data will be entered and managed using REDCap (Research Electronic Data Capture), a Web-based application for managing databases hosted at the Department of Cardiac Thoracic and Vascular Sciences, University of Padova (Italy).

#### Statistical Analysis Plan

The primary endpoint will be analyzed for the intention-to-treat (ITT) population. After having reached the sample size foreseen, a *t* test with an alpha level equal to .025 will be performed to assess the statistical differences in NB between protein-fortified diet and standard diet arms. As secondary endpoint, the hospital mortality rate will be considered. On the ITT population, the secondary endpoint will be evaluated by testing the difference between the 2 groups in a logistic model framework (alpha=.025).

The study was approved by the regional ethics committee of Friuli Venezia Giulia, Italy (CEUR-2016-Sper-066-ASUIUD). Each patient or legally authorized representative must provide written informed consent for the study procedures.

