In the critical setting, protein is the macronutrient most often lacking in such patients, and its supplementation is likely to result in beneficial effects [7]. Disorders of protein metabolism are documented as physiologic responses to stressful events and are reflected by important nitrogen loss and muscle wasting, which are proportional to the severity of illness [8]. Current evidence supports the early administration of protein supplementation because a stressful event alters homeostatic balance, resulting in an increased protein catabolism [9]. Administering exogenous protein or amino acid is crucial to reduce the breakdown of endogenous proteins by providing an alternative source of amino acids for gluconeogenesis and protein synthesis. Protein-energy deficit is associated with an increased rate of infection, poor wound healing, reduced respiratory muscle mass, and delayed weaning from mechanical ventilation, resulting in increased length of stay in ICU and increased care costs [10]. A high protein intake, estimated using a weight-based equation (1.2-2 g/kg/day), is recommended during the ICU stay regardless of the simultaneous caloric intake [9,11].

This paper presents the development of a protocol for a randomized controlled trial (RCT) aimed at assessing changes of nitrogen balance (NB) in ICU patients administered with standard parenteral/enteral diet and protein-fortified parenteral/enteral diet. Together with the study protocol, results of the pilot study conducted to assess the feasibility of such a trial are also presented.

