Although the NB was negative in all patients, we observed that cumulative NB in the first 72 hours was different among subjects observed. This is probably due to an interindividual variability in the lean body mass that results in a different amount of protein metabolism waste. Beyond its action on protein metabolism, dietary protein intake affects body composition [18]. This interindividual variability might be considered in the estimation of protein intake. However, while a high protein intake is able to preserve lean mass, especially during the early or most catabolic phases of illness, the specific goal of protein requirement to minimize the loss of lean mass is not yet clear [21,24]. Additionally, together with the marked negative NB, actual protein intake was found to be dramatically lower than that recommended by international guidelines for patients undergoing mechanical ventilation.

Weight-based equations (1.2-2 g/kg/day) may be used to monitor adequacy of protein provision [2,25], but in adult critically ill patients admitted to ICU, it is difficult to achieve this target. This is because standard nutritional formulations are rich in lipid and carbohydrate calories, but the protein content is inadequate. Furthermore, our findings showed that the contribution of EN to caloric intake remained stable over the period of observation. This may be attributable to feeding intolerance and high gastric residual volumes or to interruptions for medical procedures (eg, bronchoscopy, computed tomography, as with patient 7). If EN is insufficient, supplemental PN should be considered [9]. However, even if PN administration progressively increased during the period of observation, the composition of both PN or EN did not allow the achievement of protein optimal requirements.

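### The primary t test on nitrogen balance ignores admission weight and APACHE II, both already collected; prespecified adjustment would probably gain precision, though the planned test is valid

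*Protocol article*

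**What the plan says.** Protocol article, Statistical Analysis Plan: in the intention-to-treat population, a t "test with an alpha level equal to .025 will be performed to assess the statistical differences in NB" between the two diet arms. No covariate is named. NB is in absolute grams, as the formula under Data Collection and the design values under Sample Size show. The calculation there aims at "detecting a difference of at least –6 g of NB between the 2 groups". It takes the spread of NB to be 5 g in each arm.

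Three other places bear on the choice:

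- **Data Collection** lists weight at admission and "illness severity assessed using the Acute Physiology and Chronic Health Evaluation (APACHE) II score" as baseline items.
- **Introduction** describes "important nitrogen loss and muscle wasting, which are proportional to the severity of illness".
- **Principal Findings** says of the differences in cumulative NB between pilot patients: "This is probably due to an interindividual variability in the lean body mass that results in a different amount of protein metabolism waste".

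Treatment Arms sets the intervention arm's protein target per kg of body weight recorded at admission.

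**The concern.** By the article's own reasoning, NB should vary between patients for reasons that are partly visible at baseline. Severity is measured by APACHE II. Body size is measured by weight, which acts in two ways: as a rough stand-in for lean mass, and through a protein target that scales with it. The t test puts all of that variation into the error term.

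With 38 patients, the stake is the width of the confidence interval and some margin of power. The covariates are collected in any case, and the choice has to be made before outcome data are seen.

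**Working it through.** **Inputs.** Sample Size gives a difference of 6 g, SD 5 g in each arm, alpha .025, power 0.90, 19 per arm. Sidedness is not stated. R², the share of within-arm NB variance explained by weight and APACHE II together, is not in the documents. I assume 0 to 0.40 and show the range.

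**1. The plan's own figure.** For a two-sample t test, SE = 5 × √(2/19) = 1.62 g, noncentrality = 6/1.62 = 3.70, df = 36. At two-sided .025 the noncentral t gives power 0.908 with 19 per arm. With 18 per arm it is 0.889, so 19 is the smallest size that reaches 0.90. The stated size reproduces exactly. One-sided .025 would need only 16 per arm, so I use two-sided .025 throughout.

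**2. ANCOVA with two covariates.** Three things change:

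- the residual SD becomes 5 × √(1 − R²);
- the error df falls from 36 to 34;
- the variance of the arm difference rises, on average, by the factor 1 + 2/(38 − 2 − 3) = 1 + 2/33 = 1.061, because two slopes are estimated.

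So SE = 5 × √[(1 − R²) × (35/33) × (2/19)]. For R² = 0.20: 5 × √(0.80 × 1.0606 × 0.10526) = 1.49 g, noncentrality 6/1.49 = 4.02.

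| Analysis at 19 per arm | SE (g) | Power for 6 g |
|---|---|---|
| Unadjusted t test | 1.62 | 0.908 |
| ANCOVA, R² 0 | 1.67 | 0.888 |
| ANCOVA, R² 0.10 | 1.58 | 0.920 |
| ANCOVA, R² 0.20 | 1.49 | 0.948 |
| ANCOVA, R² 0.30 | 1.40 | 0.971 |
| ANCOVA, R² 0.40 | 1.29 | 0.987 |

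**3. Break-even.** The SEs are equal when (1 − R²) × 35/33 = 1, that is R² = 1 − 33/35 = 0.057. With the two lost df as well, power breaks even at an R² of about 0.06. At R² = 0 the loss is 0.908 − 0.888 = 0.020.

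**4. Is an R² above 0.06 plausible?** The documents give no correlation, so this is only an indication. The middle half of the feasibility patients weighed 66 to 94 kg (Table 1), a span of 28 kg. At a target of 1.2 to 2 g/kg/day, the nitrogen-intake term of the NB formula differs across that span by 28 × 1.2/6.25 = 5.4 g to 28 × 2/6.25 = 9.0 g per day if the target is met. That is at least as large as the assumed SD of 5 g. Excretion may also rise with body size and intake, and it enters the formula with the opposite sign. The net dependence of NB on weight is therefore smaller by an unknown amount.

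**The case against.** The strongest case against is that nothing is wrong. The t test is valid under 1:1 randomisation, its standard error already allows for chance imbalance, it matches the sample-size calculation, and it reaches the 90% target. All of that stands. A reader might infer that chance imbalance in a trial of 38 biases the planned test; the documents do not support that.

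Other stronger readings also fail:

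- **The article links body weight to nitrogen loss.** It does not. It names severity, and it names lean body mass with the word probably. Weight is a proxy for lean mass, and it also sets the intervention target per kg.
- **A large share of NB variance is predictable.** No correlation is given, and the spread of weight or APACHE II in the pilot says nothing about their correlation with NB.
- **Adjustment is free, or cuts the required size by about a fifth.** Once slope estimation is counted, the required size at R² 0.20 falls from 19 to 17 per arm, about a tenth. At R² 0 it rises to 20.
- **Allocation is unstratified.** The article says only that a computer algorithm is used. It is a condensed account, so silence on stratification shows nothing.

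One technical objection has some force: protein per kg is set differently in the two arms, so the slope of NB on weight may differ between arms. A common-slope ANCOVA with equal arms still targets the average difference, but its gain could be smaller than the table shows.

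It can also be said that a fuller analysis plan might add an adjusted analysis. It might, but the article does state the primary method, and that stated choice is what is at issue.

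**Conclusion.** The point holds as a recommended gain in precision. The primary analysis as stated leaves unused two baseline measures that the article's own reasoning makes likely to be prognostic. At an assumed R² of 0.20 to 0.30, the SE falls from 1.62 g to 1.49–1.40 g and power rises from 0.908 to 0.948–0.971. Below an R² of about 0.06 adjustment loses slightly, by at most about 2 points of power.

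These figures rest on the article's 6 g and 5 g, on two-sided .025, on 38 patients analysed, on a common slope in both arms, and on an R² that the documents do not give. The case for acting is that the possible loss is small and capped, while the article's account of why NB varies makes some gain likely.

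**What to change.** In the Statistical Analysis Plan, make the primary analysis an ANCOVA of NB on arm, admission weight and baseline APACHE II, in the intention-to-treat population at the same alpha. Report the adjusted difference in grams with its confidence interval. Keep the unadjusted t test as a prespecified sensitivity analysis, so that the result the sample size was built on is still reported.

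The cost is about one sentence, two error degrees of freedom and no new data. If the covariates turn out uninformative, power is 0.888 instead of 0.908. The change must be fixed before outcome data are examined by arm.
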